#### Assessment of confounders

We expect the randomization procedure to equalize risk factors across treatment groups; however, we will produce summary statistics to explore any unexpected differences in the values of covariates in the treatment groups. While we do not expect differences in covariates in the treatment groups, it is likely that the response groups will differ on some relevant clinical variables (for example, comorbid conditions). Thus, we will formally assess response group differences in possible covariates of interest and incorporate any covariates identified that are considered both statistically and clinically relevant as additional main effects for the analyses of response predictors and moderators.

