### Major endpoints

The primary outcome is mean change on the CAPS past-week score between the two treatment arms. Secondary outcomes include response and remission on the CAPS past-week score. Response is defined as ≥ 50% reduction from the baseline CAPS total score at the final on-drug study visit (V9 for completers). Remission is defined as a CAPS score ≤ 20 at the final on-drug visit.

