### Moderator analyses

We have *a priori* specified factors that we expect may moderate the treatment effect in PTSD subjects [47]. These include, age, type and age of trauma exposure, and past treatment history. While the study is not specifically powered to detect these effects, we will analyze treatment by subgroup interaction effects in these exploratory analyses in order to provide important information for the design of future, more definitive studies. We will determine significant moderators by specifically testing the treatment by variable interaction added to the analysis of the primary outcome. Given the limited sample size, each possible moderator will be analyzed separately.

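### Adjustment covariates for the exploratory predictor and moderator models are chosen by testing them against the observed response, so their own p-values are not valid evidence of prediction

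*Protocol article*

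**What the plan says.** Assessment of confounders treats two comparisons differently.

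- **Between treatment groups**, the check is descriptive: "we will produce summary statistics to explore any unexpected differences in the values of covariates in the treatment groups".
- **Between response groups**, differences are expected: "it is likely that the response groups will differ on some relevant clinical variables (for example, comorbid conditions"). They are then tested and acted on: "we will formally assess response group differences in possible covariates of interest and incorporate any covariates identified". The condition and the use follow: "considered both statistically and clinically relevant as additional main effects for the analyses of response predictors and moderators".

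The section gives neither a closed list of candidates nor a significance threshold; comorbidity is only an example. Major endpoints defines response as a fall of at least 50% in CAPS total from baseline at the last on-drug visit. The screening variable is therefore a dichotomised form of the primary outcome.

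Moderator analyses works differently. There the factors are named beforehand: "We have *a priori* specified factors that we expect may moderate the treatment effect in PTSD subjects". The list follows: "These include, age, type and age of trauma exposure, and past treatment history". Each is tested through its interaction with treatment, added to the primary-outcome model. The section calls this exploratory and says the study is not powered for it.

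**The concern.** Response is observed after randomisation. Screening covariates against it and then modelling it, or the CAPS score it is cut from, uses the same data twice. This has two consequences.

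1. A covariate enters the model because it happened to differ between responders and non-responders in this sample. Its p-value in the later model no longer has its nominal meaning.
2. A factor that truly predicts outcome but misses the threshold is left out. A variable correlated with it can then pick up its effect.

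The adjustment set therefore varies with chance. The article has a stated interest in variables that predict or mediate change, and it wants the exploratory results to inform later, more definitive studies. Covariate effects read off these models could be carried into that planning with more weight than they deserve.

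**Working it through.** **Inputs from the article.** Statistical power/sample size gives 50 completers per group and 35% dropout: 50/(1 − 0.35) = 76.9, so 77 per group and 154 in total, as stated. This supplies the 100 completers used below. The article gives no figure for the covariate rule itself.

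**Assumptions, not in the article.** Screening is at 0.05 with 5 to 30 candidates unrelated to outcome, and 40% to 45% of patients respond. Linear or logistic models stand in for the mixed models. The clinical-relevance filter is not modelled.

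**Step 1: chance of a false selection.** For K independent null candidates, P(at least one kept) = 1 − 0.95^K, and the expected number kept is 0.05 × K.

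| K | P(at least one) | Expected number |
|---|---|---|
| 5 | 0.23 | 0.25 |
| 10 | 0.40 | 0.5 |
| 20 | 0.64 | 1.0 |

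Simulation agreed: 0.23, 0.40 and 0.65. With ten candidates correlated at 0.3 the chance was about 0.36.

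**Step 2: what a kept null covariate shows in the later model.** The screen compared responders with non-responders by t-test. Kept covariates were then added to a model with treatment, a moderator and their interaction.

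- Same binary response, logistic model: p<0.05 again in 85%, 78% and 76% of kept covariates for K = 5, 10 and 20.
- Continuous outcome, 40% responders: 39%, 40% and 39% for the same K, and 26-28% with ten candidates correlated at 0.3.
- Continuous outcome, 45% responders: 42%, 39% and 37% for K = 10, 20 and 30.

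A null covariate fixed in advance would show p<0.05 in 5%. The continuous-outcome rates are lower because dichotomising CAPS discards information, so the second test is only partly a repeat of the first.

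**Step 3: a real factor that the screen can miss.** A null predictor was correlated 0.4 to 0.6 with a truly prognostic factor that entered the model only if it passed the screen. The predictor's type I error was about 7-12%, against about 5% when the factor was always included. The result depends on the assumed strength of the factor. A strong factor is rarely missed, and the error then moves back towards 5%.

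**Step 4: what is not damaged.** After the screen, the type I error of the treatment-by-moderator interaction was 0.051-0.053 (continuous) and 0.043-0.053 (binary). The moderator's main effect, where the moderator was not itself chosen by the screen, was 0.045-0.055.

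**The case against.** The strongest reply is that the selected covariates are adjusters, not findings. The text enters them as extra main effects in models of other variables and nowhere says that they will be reported as predictors. A reader might infer that the plan screens predictors on response and then confirms them on the same data. The article does not say so: it uses the word confirmatory only for the PSS-SR, CGI and SDS analyses. The invalid p-values matter only if someone interprets a screened covariate's own coefficient.

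That reply stands as a limit on the point, but it does not remove it. The omission effect in Step 3 falls on the variable under study, whether or not the adjusters are interpreted.

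A second reply is that the false-flag rate per candidate is low. With the continuous outcome it is about 0.05 × 0.40 = 0.02. That is correct, but the reader of a fitted model sees only the covariates that were kept, and without a closed list cannot tell how many were tried.

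Three further points on the other side also hold:

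- Requiring clinical relevance would reduce the number selected.
- A reader might think the list cannot be settled before unblinding. Response is defined from CAPS alone, so a pooled screen needs no treatment codes. The list depends on outcome data, not on unblinding.
- A covariate list is often left to the analysis plan. Here, however, the article states a selection rule, and an analysis plan that followed it would keep the problem.

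**Conclusion.** The point holds in a limited form and is a cheap improvement. The rule chooses adjustment covariates by their association with the outcome that is then modelled. For kept null covariates, the chance of p<0.05 is about 26-42% (continuous outcome) or 76-85% (same binary response) instead of 5%. The error of a correlated null predictor can rise to about 7-12%. These sizes rest on the assumed threshold, number of candidates, response rate and prognostic effects, none of which the article gives.

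Two stronger conclusions are not supported. First, the moderator tests are not invalidated: the factors are named in advance, the interaction keeps close to its nominal error, and the statement that "each possible moderator will be analyzed separately" is not at fault. Second, the efficacy conclusion is not at risk: the rule is confined to predictor and moderator models, so the primary CAPS comparison, its 0.05 level and the sample size are untouched.

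**What to change.** In Assessment of confounders, replace the responder screen with a short list of baseline covariates, fixed before any outcome data are examined and used in every predictor and moderator model. Suitable content is:

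- the baseline CAPS past-week score;
- site, since randomisation is blocked by site;
- a few named baseline clinical variables, such as comorbidity, which the article already expects to differ by response.

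Keep the comparison of responders with non-responders as a descriptive table, and state that it will not be used to choose model terms.

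The change is one of wording. It costs a few degrees of freedom for covariates that may prove unimportant, and it needs no new data, since these variables are collected before treatment.

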### Site effects

Our assumption for the analysis plan and power calculations is that the protocols will be implemented with sufficient consistency to avoid significant site effects in the results. Given that the randomization will be blocked by site, there is no reason to believe that the subjects will have a different *a priori* probability of response or will be significantly different from a clinical perspective. However, we will test for site differences in all outcome measures with appropriate univariate comparisons to ensure that site is not a significant confounder. If there is evidence of significant site differences in response outcomes, we will proceed with stratified analyses in place of the proposed analyses.

#### Secondary aims

##### Response rates

We will use a mixed effects model for the binary response data (generalized linear mixed model or GLMM) where, at each time point, a subject will be classified as a responder if there is at least 50% improvement in CAPS compared to the baseline measure. The factors in the model will be the same as for testing the primary hypothesis above. This analysis is an averaged group comparison of time-point specific response rates, and thus a patient can change response categories over time. We anticipate observing a significant group-by-time interaction and will perform *post hoc* tests by time point to estimate when a significant divergence in response rates occurs.

### Depressive symptoms

We will use the same approach as for the primary analysis of the CAPS as a continuous variable as described above, except using MADRS as the dependent variable.

#### Safety and tolerability

We will statistically test the equivalence of various possible adverse events (for example, headache, insomnia) from the PRISE and FIBSER using a test of the group effect in either logistic or Poisson regression models, depending on whether the outcome is a count or a binary measure. We will also compare time to dropout as well as first adverse event in both groups using a log-rank test of Kaplan-Meier curves to determine the possible effect of adverse events on the course of treatment response.

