Increased activity of CRH-containing neurons in the amygdala activates fear-related behaviors [9], while neocortical CRH may reduce reward expectation [10]. Intracerebroventricular administration of CRH produces anxiety-like behaviors in animal models, including features particularly relevant to PTSD such as sleep disturbance, enhanced acoustic startle response, and increased conditioned fear responses. CRH type 1 receptor (CRHR1) antagonists reverse stress-related behaviors in preclinical models, including the elevated plus-maze, defensive withdrawal, light/dark transfer, and conditioned fear paradigms [11]. Animal models of early life stress have been associated with hyperactivity of CRH neurons, with chronic activation of CRHR1 in limbic brain regions [12,13]. Mice deficient in CRHR1 display decreased anxiety-like behavior and an impaired stress response [14]. Startle reactivity in mice depends on reciprocal interactions between CRH and norepinephrine systems [15]. In PTSD patients, increased cerebrospinal fluid CRH concentrations were found with single lumbar puncture sampling [16,17] as well as throughout a 24-hour period [18]. In addition, PTSD has been associated with increased psychophysiological responses, such as startle, skin conductance, and heart rate reactivity [19]. Recent studies using fear conditioning methods have found that PTSD patients have impaired inhibition of fear [20] and deficits in fear extinction [21].

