### Randomization

Randomization occurs at Visit 3. To prevent confounding of the biological measures by the dexamethasone dose on the night before Visit 3, baseline laboratory and ECG tests are conducted the day prior at Visit 2. At Visit 3, upon completion of the post-dexamethasone venipuncture, participants are assessed with the CAPS, MADRS, C-SSRS, and CGI-S. To be eligible for randomization, participants have to score ≥ 50 on the CAPS rating for both the past week and the past month at this visit. At this visit subjects also complete the PSS-SR, QIDS-SR, the Pittsburgh Sleep Quality Index (PSQI) [40], Brief Pain Inventory (BPI) [41], and Patient Rated Inventory of Side Effects (PRISE) [42]. Self-reported functioning is assessed using the Sheehan Disability Scale (SDS) [43]. To assess the impact of recent significant life events, participants also complete the Life Experiences Survey (LES) [44].

Participants who meet all inclusion and no exclusion criteria are eligible for randomization. Treatment assignment lists, generated using randomized permuted blocks for each site, are used at each site to ensure equal allocation across treatment groups across the sites and at any time during the study. These lists were individually printed, placed in sealed opaque envelopes by the study biostatistician, and then delivered directly to the Investigational Drug Pharmacy personnel at each site. When a participant completes all procedures necessary for randomization, the study physician at each site notifies the pharmacy personnel, who assign the patient to the treatment group indicated on the randomization list.

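### The PRISE safety test names only a group effect and gives the pre-drug PRISE no role, so symptoms already present at baseline can dilute a drug-caused difference

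*Protocol article*

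**What the plan says.** The Safety and tolerability section (under Secondary aims) takes possible adverse events as its outcomes and sets out their source and the test in these words: "for example, headache, insomnia) from the PRISE and FIBSER using a test of the group effect in either logistic or Poisson regression models", the choice of model "depending on whether the outcome is a count or a binary measure". The section names no baseline covariate, no change from baseline and no rule for when a reported symptom counts as an event. It does not say which visits enter.

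PRISE is collected before any drug is taken. The Randomization section states "Randomization occurs at Visit 3" and lists among the forms completed at that visit the "Brief Pain Inventory (BPI) [41], and Patient Rated Inventory of Side Effects (PRISE) [42". Table 1 also marks PRISE at screening, and then at Visits 4, 5, 6 and 9. FIBSER starts at Visit 4, so it has no pre-drug value.

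Two other parts of the article bear on the insomnia example:
- The Background, describing effects of CRH in animal models, refers to "features particularly relevant to PTSD such as sleep disturbance, enhanced acoustic startle response, and increased conditioned fear responses".
- Inclusion criterion 3 in Table 2 requires a CAPS score of at least 50 at screening and at Visit 3, so every randomized woman is symptomatic when the drug starts.

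**The concern.** A symptom inventory completed before treatment will pick up symptoms of the illness. In this population insomnia is a likely one. Exclusion criterion 6 also exempts zolpidem, eszopiclone and zaleplon, so women using sleep medication can enter.

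If the outcome is simply whether an item is reported on treatment, a woman whose insomnia predates the drug and continues unchanged counts as an event in her arm. Such events occur in both arms and carry no information about the drug, but they add variance and crowd out the new cases. If the drug also relieved pre-existing insomnia in some women while causing it in others, the two effects would partly or wholly cancel.

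Safety is part of the primary aim (AIMS section), and the safety sentence frames its test as one of equivalence. An insensitive, non-significant comparison could therefore be read as similar tolerability.

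**Working it through.** **The plan's own figure.** The article states no figure for the safety comparison. Its sample size reproduces: 50 completers / (1 − 0.35) = 76.9, rounded up to 77 per arm, and 2 × 77 = 154. I use 77 per arm.

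**Assumptions, none of them in the article.** Let b be the share of women reporting insomnia at Visit 3, s the share of those who still report it on treatment (same in both arms), and q the new-onset rate among women free of it at Visit 3. The base case is b = 60%, s = 80%, q = 25% on drug and 5% on placebo, with b varied from 40% to 75%.

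**Formulas.**
- Any on-treatment report: p = b·s + (1 − b)·q.
- Treatment-emergent, all women in the denominator: p = (1 − b)·q.
- Treatment-emergent, only women free of insomnia at Visit 3: p = q, with n = 77·(1 − b).
- Power, two-sided 5%: Φ[(d − 1.96·√(2·p̄·(1 − p̄)/n)) / √((p1(1 − p1) + p2(1 − p2))/n)], where d is the difference and p̄ the mean of the two proportions.

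**Base case, b = 60%.**
- Any report: drug 0.48 + 0.40 × 0.25 = 0.58; placebo 0.48 + 0.40 × 0.05 = 0.50. Power = Φ[(0.08 − 1.96 × 0.0803)/0.0801] = Φ(−0.97) ≈ 17%. A simulated unadjusted logistic test gave 16%.
- Treatment-emergent, all women: 0.10 against 0.02. Power = Φ[(0.08 − 1.96 × 0.0383)/0.0377] = Φ(0.13) ≈ 55%.
- Treatment-emergent, women free at Visit 3 (n = 30.8): 0.25 against 0.05. Power = Φ[(0.20 − 1.96 × 0.0910)/0.0873] = Φ(0.25) ≈ 60% (61% by simulation).

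The first two comparisons have the same 8-point difference. The treatment-emergent count gains because it removes the persisting cases that both arms share.

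**Over the range of b (normal approximation).**

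| Baseline prevalence | Any on-treatment report | Treatment-emergent, all women | Treatment-emergent, free at Visit 3 |
|---|---|---|---|
| 40% | 33% | 74% | 78% |
| 60% | 17% | 55% | 60% |
| 75% | 9% | 37% | 41% |

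**Second set of assumed rates** (new onset 30% on drug, 10% on placebo; s = 80%; 77 per arm). Power for any report against treatment-emergent with all women in the denominator:
- b = 0: 0.88 and 0.88, so no loss
- b = 30%: 0.43 and 0.71
- b = 50%: 0.23 and 0.54
- b = 70%: 0.12 and 0.35

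With 50 per arm and b = 50% the pair is 0.17 and 0.38.

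**The covariate alternative**, same second set, simulated logistic model with group only against group plus baseline status:
- b = 30%: 0.44 and 0.62
- b = 50%: 0.23 and 0.36
- b = 70%: 0.12 and 0.16

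With no drug effect, both models rejected in about 4-6% of runs.

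**Cancellation.** In the second set at b = 50%, let the drug lower persistence to 60%. Drug: 0.5 × 0.6 + 0.5 × 0.3 = 0.45. Placebo: 0.5 × 0.8 + 0.5 × 0.1 = 0.45. The difference disappears, although new onset is 30% against 10%.

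**The case against.** The strongest reply is that this rests on silence. The safety text is a short summary in a journal article, and an event definition or baseline covariate may sit in the full protocol or analysis plan. Taking PRISE before the drug fits an intention to use it. A reader might infer that the plan commits to comparing raw on-treatment counts; it does not. It allows a binary outcome and fixes neither the visits nor the handling of baseline. That much of the reply stands.

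It does not remove the point. The article does state how baseline enters for other outcomes: response is defined against baseline, the startle analysis targets the group-by-time interaction, and the cortisol analysis adjusts for the Day 1 level. The safety analysis is described at a similar level of detail, yet only a group effect is named.

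Other parts of the reply also stand:
- A reader might infer that the comparison is biased or that drug-caused effects will be hidden. Randomization balances pre-existing symptoms in expectation and the error rate stays near 5%. The harm is lost sensitivity.
- The rates are assumed. The Background lists fatigue and somnolence, not insomnia, among the drug's commonly reported adverse events.
- PRISE is not the only safety evidence. The plan also compares time to first adverse event and time to dropout, and the PSQI measures sleep with a Visit 3 value.
- A reader might infer that resolution of adverse effects cannot be followed because PRISE is absent at Visits 10 and 11. Table 1 and the Follow-up period section schedule adverse events at both visits, and Table 1 adds FIBSER. Resolution is monitored.

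**Conclusion.** The point holds in a limited form. The stated PRISE analysis names only a group effect and gives the pre-drug PRISE no role, in a population symptomatic at entry and with an example item that overlaps with the disease. If baseline is in fact ignored, the comparison remains valid but loses sensitivity for items common before treatment. In the base case power is about 16-17%, against about 55-61% for treatment-emergent events. The loss grows with baseline prevalence and is nil for items absent at Visit 3. These figures illustrate the mechanism; the true loss is unknown because the article gives no baseline prevalence, persistence or onset rates, and 77 per arm makes no allowance for dropout. The point does not extend to FIBSER.

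**What to change.** In the Safety and tolerability section, state that PRISE items are analysed as treatment-emergent: absent at Visit 3, or worse than at Visit 3. The article does not describe how PRISE items are graded, so what counts as worse needs defining against the form. State also whether the denominator is all randomized women or those free of the item at Visit 3. At the least, include the Visit 3 PRISE value as a covariate in each logistic or Poisson model; this recovers less power, especially when baseline prevalence is high.

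The cost is a sentence or two of text. The Visit 3 data are already collected, and no visit or form is added.

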### Psychophysiological testing

For the fear-potentiated startle paradigm, the mean startle magnitude for each CS type in each block will be used to calculate percent change scores with the following formula using noise alone (NA) trials as the reference:

$$\begin{array}{ll} \mathrm{Percent}\mathrm{potentiation} & =100*\left(\mathrm{CS}\;\mathrm{startle}\;\mathrm{magnitude}\right)\\ & –\;\left(\mathrm{NA}\;\mathrm{startle}\;\mathrm{magnitude}\right)\\ & /\left(\mathrm{NA}\;\mathrm{startle}\;\mathrm{magnitude}\right) \end{array}$$

Discrimination between danger and safety signals will be calculated as the difference in potentiation between CS + and CS − trials. Fear inhibition will be assessed as the difference between the reinforced trials during conditioning (AX+) and the transfer trials containing elements of CS + and CS − (which are AB trials). Finally, fear extinction will be measured as the decrease in response to the CS + during the extinction session. Given the assumption of significant individual variation in the psychophysiological measures, we will perform mixed effects linear models comparing treatment group for each fear-potentiated startle measure (conditioning, discrimination, transfer of safety, and extinction) with Block, Time (baseline versus six weeks) as the within-subjects factor and Group (GSK561679 versus placebo) as the between-subjects factor and including a random intercept. The effect of interest will be the group*time interaction, indicating a significant difference between groups in change in startle over time. Skin conductance response will be analyzed in a parallel manner. Contingency awareness will be analyzed by comparing US-expectancy ratings for each CS trial type in a parallel manner.

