The acoustic startle response (eyeblink component) is measured via electromyography (EMG) of the right orbicularis oculi muscle. Two 5 mm Ag/AgCl pre-gelled disposable electrodes are positioned approximately 1 cm under the pupil and 1 cm below the lateral canthus. All resistances are less than 6 kilo-ohms. EMG activity is acquired at a sampling rate of 1 kHz, amplified and digitized using the EMG module of the Biopac system. The peak amplitude of the EMG measured between 20 and 200 ms after startle probe onset is used as the measure of startle magnitude. The skin conductance level (SCL) is acquired at a sampling rate of 1 kHz using the GSR module of the Biopac system. Two 5 mm Ag/AgCl disposable electrodes filled with isotonic paste are attached to the hypothenar surface of the palm of the non-dominant hand. The average SCL during the three to six seconds after CS onset will be subtracted from the one second pre-CS baseline to calculate skin conductance response (SCR).

To assess subject awareness and US expectancy during each experimental session subjects respond on a response keypad (SuperLab, Cedrus Corp.) during the presentation of each trial. During both fear conditioning and extinction sessions subjects press a button marked ‘+’ if they expect a CS to be followed by the US, a button marked ‘−’ if they do not expect a CS to be followed by the US, and a button marked ‘0’ if they are uncertain of what to expect.

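### The startle model names only a random intercept, so for block-scored measures the group-by-time standard error is too small whenever responses vary between sessions within a subject; the effect of interest for extinction also needs stating

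*Protocol article*

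**What the plan says.** All references are to the protocol article.

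- **Design of the test** (Pre-randomization assessments, 1. Psychophysiological testing): each subject is tested twice, at Visit 1 and at Visit 7. A session has three conditioning blocks and six extinction blocks. The transfer test has three AB trials, with no blocks described.
- **Unit of outcome** (data analyses, Psychophysiological testing): "the mean startle magnitude for each CS type in each block will be used to calculate percent change scores".
- **Model** (same section): one mixed linear model for each of conditioning, discrimination, transfer of safety and extinction, with Block and Time "as the within-subjects factor and Group (GSK561679 versus placebo) as the between-subjects factor and including a random intercept". No other random term and no residual covariance is named. Skin conductance and expectancy ratings are to be handled the same way.
- **Test**: "The effect of interest will be the group*time interaction, indicating a significant difference between groups in change in startle over time".
- **Extinction**: "fear extinction will be measured as the decrease in response to the CS + during the extinction session".
- **Scores**: startle magnitudes "will be used to calculate percent change scores with the following formula using noise alone (NA) trials as the reference", but the printed formula has no bracket around the difference CS − NA. For skin conductance, the section describing the test says: "The average SCL during the three to six seconds after CS onset will be subtracted from the one second pre-CS baseline".
- **Timing**: the analysis section labels the second time point as six weeks. Table 1 places Visit 7 at week 5, day 35.

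**The concern.** Group-by-time asks whether the change from one session to the other differs between arms. Its error must therefore include how much individual subjects' true change varies around their arm's mean. A lone random intercept gives two blocks from the same session no more correlation than two blocks from different sessions. It is correct only if subjects in an arm do not differ in their session-to-session change. That is hard to defend when the sessions are 42 days apart (day −7 to day 35) with five weeks of treatment in between.

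A second issue concerns extinction, which is defined as a decline within a session. If block-level scores are modelled, group-by-time averages over blocks, and a drug effect on the decline sits in group-by-time-by-block.

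Fear conditioning and extinction head the list of secondary aims, and the Discussion expects mechanistic insight even if the drug does not beat placebo. Too-small standard errors would produce mechanistic findings more often than the nominal 5%, and the wrong contrast could miss a real effect on extinction. The false discovery rate adjustment planned for secondary outcomes takes valid P-values as its input and does not repair this.

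**Working it through.** The article states no power, error rate or variance for the psychophysiology analysis, so there is no figure to reproduce.

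**Inputs from the article.** K = 3 blocks (conditioning, and discrimination derived from it), K = 6 (extinction, if scored by block), K = 1 (transfer, no blocks described); two sessions per subject; 50 completers per group, borrowed from the CAPS sample size section; alpha 0.05, taken as two-sided.

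**Assumed, not in the article.** The session share of within-subject variance, ρ = σs²/(σs² + σe²), where σs² is subject-by-session variance and σe² is block residual variance. It is varied from 0 to 0.5, scaled so that σs² + σe² = 1. Data are balanced, with group, time and block fully crossed as fixed effects.

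**True variance of group-by-time.** A subject's difference between session means has variance 2(σs² + σe²/K). With n per group, the group contrast has variance (4/nK)(σe² + Kσs²).

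**Variance the random-intercept model uses.** It replaces the bracket with the pooled within-subject mean square. Per subject this pools one between-session degree of freedom with 2K − 2 block degrees of freedom:

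[(σe² + Kσs²) + (2K − 2)σe²]/(2K − 1) = σe² + Kσs²/(2K − 1).

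The ratio of reported to true SE is the square root of [σe² + Kσs²/(2K − 1)]/[σe² + Kσs²]. It does not depend on n. Type I error ≈ 2[1 − Φ(1.96 × ratio)].

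**Example, ρ = 0.2.**
- K = 3: true 0.8 + 0.6 = 1.4; model 0.8 + 0.6/5 = 0.92; ratio √(0.92/1.4) = 0.81; type I error 0.11.
- K = 6: true 0.8 + 1.2 = 2.0; model 0.8 + 1.2/11 = 0.909; ratio √(0.909/2.0) = 0.67; type I error 0.19.
- K = 1: both brackets equal σe² + σs², so the ratio is 1 and there is no inflation.

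**Range** (simulated values from 5,000 trials per setting):

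| ρ | K = 3: SE ratio | type I, formula | type I, simulated | K = 6: SE ratio | type I, formula | type I, simulated |
|---|---|---|---|---|---|---|
| 0 | 1.00 | 0.05 | 0.045 | 1.00 | 0.05 | 0.049 |
| 0.1 | 0.89 | 0.08 | 0.087 | 0.80 | 0.12 | 0.126 |
| 0.2 | 0.81 | 0.11 | 0.110 | 0.67 | 0.19 | 0.185 |
| 0.3 | 0.74 | 0.15 | 0.143 | 0.59 | 0.25 | 0.245 |
| 0.5 | 0.63 | 0.22 | 0.210 | 0.47 | 0.36 | 0.366 |

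In the same simulations, comparing the change in session means between groups rejected in 0.047 to 0.056 of trials at every ρ.

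**Extinction contrast.** Illustration with K = 6: the drug alters only the within-session decline, by 0.15 per block on the scale above, leaving the session mean unchanged. A correctly calibrated group-by-time test on level rejected in about 0.05 of trials, that is, no more than by chance. A test of the change in per-session slope rejected in 0.59 (ρ = 0) and 0.70 (ρ = 0.2; higher because block residual variance is smaller there).

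**Formulas as printed.** With illustrative CS = 150 and NA = 100, the printed expression is 100 × 150 − 100/100 = 14,999; with the bracket, 100 × (150 − 100)/100 = 50%. With illustrative baseline 5.0 and CS-period level 5.6, the worded skin conductance response is 5.0 − 5.6 = −0.6; the usual sign gives +0.6. Reversing the sign of every score leaves |t| and P unchanged.

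**The case against.** The article says the model includes a random intercept; it does not say that nothing else is in it. The primary analysis section names SAS PROC MIXED for continuous variables, where a residual covariance can be added, and an analysis plan that is not shown may do so. That is fair, and it is a reason to ask for clarification. It does not change what the text specifies: one random term and a test that this term alone does not support.

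A reader might infer that blocks are treated as wholly independent replicates. They are not. The intercept absorbs correlation between blocks of one subject, and what is missing is the extra correlation within a session.

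A reader might also infer that extinction is not tested at all. The documents do not support that. Extinction is defined as a decrease, and if one decrease score per session is modelled, group-by-time is the correct term and the six-block inflation figures fall away for extinction. Listing Block as a factor favours the block-level reading, but the text does not settle it.

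Finally, the formula errors might be read as invalidating the scores. The text around the first makes the intended percent change plain, and the second reverses direction only. The six-week label may simply count the 42 days between sessions. These are wording slips.

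On importance, fear conditioning is a secondary aim in the Aims section, but Table 1 lists startle testing under exploratory aims and the analysis follows an exploratory heading.

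**Conclusion.** The point holds for the block-scored measures: conditioning and discrimination, and extinction if it is scored by block. It carries over to skin conductance and expectancy ratings if these are also analysed by block. On the model as written, the group-by-time standard error is too small whenever subject-by-session variance exceeds zero. The direction follows from the algebra. The size does not come from the article: it rests on an assumed session share of 0 to 0.5, giving type I error of 0.05 to about 0.22 with three blocks and 0.05 to about 0.36 with six. At a share of zero there is no inflation. The claim supported is false positives above the nominal rate, not that spurious findings are probable. Transfer is not affected.

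For extinction the text leaves open which outcome is modelled, and the right contrast depends on it. The conclusion does not extend to the whole psychophysiology plan, nor to the primary CAPS analysis or the sample size of 154.

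**What to change.** 1. Add a random subject-by-session effect to the block-level models, or reduce each session to one score and compare the change between groups. Either restores about 5% under the assumptions above.
2. State the extinction outcome. Either model a per-session decrease score with group-by-time and no Block factor, or model block-level scores and make the linear group-by-time-by-block trend the effect of interest. The trend test needs an error term that allows slopes to vary by subject and session; a per-session score handles this directly.
3. Correct the wording: percent potentiation = 100 × (CS − NA)/NA; skin conductance response = CS-period level minus pre-CS baseline; Time = baseline versus week 5 (Visit 7).

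The cost is analysis code and text. No new data and no change in trial conduct are needed. Standard errors for the block-scored measures will be larger where session variance exists.
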